## Discussion

Due to the broad distribution of recent advances in DBS technology, the implementation of directional DBS is feasible in standard care for Parkinson’s disease patients. This may lead to an increase in programming time and effort, possibly constituting an added burden for patients and clinicians alike [9]. For clinical practice, it would be of added value to know whether directional DBS leads to a clinical improvement in patients who already experience a good effect from ring-mode DBS, and in patients who experience a sub-optimal effect from ring-mode DBS. In order to investigate whether the use of directional STN DBS has a more beneficial effect on the motor symptoms of Parkinson’s disease when compared to ring-mode DBS, we use a randomised, double-blind crossover trial design. Some of the choices made in the study protocol warrant discussion.

First, we discuss performing three separate analyses for responders, non-responders and these two study populations pooled together. It is possible that there is a difference in added value of directional STN DBS when compared to ring-mode STN DBS for responders but not for non-responders, or vice-versa. Another possibility is that both responders and non-responders have added benefit from directional STN DBS, but to a different degree. Pooling responders and non-responders allows for a representative sample of the entire patient population of patients with Parkinson’s disease who received DBS treatment. If a significant difference is found between directional and ring-mode settings in the favour of directional STN DBS, this would mean we could implement directional STN DBS as the new treatment standard. Additionally, the pooled analysis will have greater power due to the higher number of subjects.

A second relevant issue is that it was not required for randomisation to have directional setting bilaterally. This approach was chosen because the most often cited reason to employ directionality is the occurrence of stimulation-induced adverse-effects [9]. These adverse-effects are not necessarily present at both sides within therapeutic current amplitudes. Another reason to opt for this approach is that a comprehensive directional monopolar review is a time-consuming effort, which can be burdensome for the patient. Hence, we anticipated that this approach warrants the best external validity.

Third, a randomised double-blind crossover trial design was chosen to answer the research question: each patient will receive both directional and ring-mode DBS treatment for a period of two months (56 days) with an accepted range of 28 to 66 days. This range was chosen, as some patients found it difficult to continue with a DBS stimulation setting (*e.g.*, ring-mode DBS) for two months if the other setting (*e.g.*, directional DBS) felt significantly better. The aim of the current study is that all patients receive a DBS setting for two months; however, if they are unable to endure the DBS stimulation setting or if there are logistical issues, then these patients will be assessed earlier. In any crossover trial, the possibility of carry-over effect should be considered. In STN DBS for Parkinson’s disease, relatively short washout periods have been reported for motor symptoms such as bradykinesia. The UPDRS motor score of STN DBS Parkinson’s disease patients was shown to worsen 90% after two hours in medication and stimulation-off condition, with axial signs worsening after three to four hours [19]. In addition to this ‘fast washout’, a slower decline of the residual effect in off-stimulation condition may occur [20]. Little is known about possible longer lingering effects. We do not implement a washout period in off-stimulation condition in this study, as we expect most of the clinical effects of the previous setting to wane within the first hours of stimulation switch. We expect that most, if not all carry-over effects will have disappeared after the minimum follow-up period of four weeks. We expect that the used settings will have had a representative effect on the participants’ symptoms, adverse-effects, and quality of life in each of the treatment periods in the crossover setting.

In the current study, only the used contact configuration, polarity and current amplitude can be adjusted. Pulse width and pulse frequency are not adjusted during the trial. In clinical practice, situations may occur when all these variables are changed in the optimisation process. However, adjusting these variables would hinder judgement of the net effect of directional DBS. Directional stimulation settings were found through the method of directional monopolar review and adjusted according to clinical insights. No imaging techniques such as prediction of volume of tissue activated (VTA) or diffusor tensor imaging (DTI) were used to assist on determining the stimulation settings.

The possible outcomes of the STEERING-trial are likely to have clinical consequences. If a beneficial effect of directional DBS is demonstrated in the responder subgroup, this means that good responders can do even better with directional DBS. If non-responders perform better with directional DBS, this might mean that’non-response’ can be caused by suboptimal electrode placement or limiting adverse-effects. If a beneficial effect of directional DBS is demonstrated in the responder subgroup, an argument can be made for performing a directional monopolar review in all patients in the weeks/months following surgery, to then implement directional stimulation standardly. If no beneficial effect of directional DBS is demonstrated, the current method of using ring-mode DBS on devices capable of directional stimulation can be continued. Directionality will still be an important tool for troubleshooting in individual patients, as its usefulness in these conditions has been previously described [11].

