**Discussion:**

The STEERING trial will provide insights into whether or not directional DBS should be standardly used in all Parkinson’s disease DBS patients or if directional DBS should only be used in a case-based approach.

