### Statistics

The sample size calculation was carried out separately for the responder group and the non-responder group. The minimum clinically important differences between ring-mode and directional DBS for the responder and non-responder groups, respectively, were three points and five points on the MDS-UPDRS-ME [16, 17]. For the responder group, we calculated a required sample size of 58 patients (29 patients in each sequence group) to detect an intra-individual difference of three points on the MDS-UPDRS-ME in off-medication state with an assumed intra-individual standard deviation (SD) of 10, 80% power and at 5% significance level. For the non-responder group, we calculated a required sample size of 34 patients (17 patients in each sequence group) to detect an intra-individual difference of five points on the MDS-UPDRS-ME in the off-medication state with an assumed intra-individual standard deviation (SD) of 10, 80% power and at 5% significance level. Considering a drop-out rate of 10% in each group, 64 responders and 38 non-responders will be included. The total sample size will be 102 patients.

Statistical analysis will be based on the intention-to-treat principle. In all analyses, statistical uncertainties will be expressed in 95% confidence intervals (CI). The primary outcome is the difference between ring-mode and directional DBS settings on the off-medication state MDS-UPDRS-ME. This analysis will be performed for responder and non-responder groups separately and for the total study population (*i.e.*, responders and non-responders pooled). Paired t-tests will be used to assess these differences, or, if not normally distributed, a Wilcoxon signed-rank test. Differences will be considered significant at *p* < 0.05 without correcting for multiple comparisons.

It is unlikely that the cross-over will have a sequence effect since the primary outcome is an objective outcome measure and will not be influenced by the patient's perspective. However, the possibility of a sequence effect cannot be ruled out. A possible sequence effect will be evaluated descriptively, as a statistical analysis cannot verify this effect [18].

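### The plan raises a different benefit in responders and non-responders, but none of its stated analyses estimates that difference

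*Protocol article*

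**What the plan says.** The abstract's discussion gives the purpose as learning whether directional DBS should be standard for everyone or "if directional DBS should only be used in a case-based approach". The Discussion justifies three analyses by the possibility of benefit in one group and not the other, or of unequal benefit: "Another possibility is that both responders and non-responders have added benefit from directional STN DBS, but to a different degree".

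For the primary outcome, the Statistics section says: "This analysis will be performed for responder and non-responder groups separately and for the total study population". Each comparison is a paired t-test (or Wilcoxon signed-rank test) at p < 0.05, "without correcting for multiple comparisons". The mixed model is described only as a check on robustness and a way to address missing data. Responder status is the randomisation stratum (Study procedures and randomisation).

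The Discussion also states consequences. In its text on pooling, a significant result favouring directional DBS could make it the new standard. Later, benefit in responders is said to support directional review in all patients. If no benefit is shown, ring-mode use can continue.

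**The concern.** Benefit in one group only, or benefit to different degrees, is a statement about the difference between two effects. Two within-stratum tests and a pooled mean do not estimate that difference. A significant result in one stratum and a non-significant result in the other can arise from chance and unequal power alone, and the strata here differ in size (58 and 34). If such a pattern were read as differential benefit, the published answer on who gains from directional DBS could reflect sample size and not patients. A pooled result that is significant beside one null stratum pulls towards both answers at once, and the article does not say how it would be read.

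**Working it through.** **Inputs (Statistics section).** The important differences "were three points and five points on the MDS-UPDRS-ME" for responders and non-responders respectively, "with an assumed intra-individual standard deviation (SD) of 10", "80% power and at 5% significance level". Evaluable numbers are 58 and 34, and enrolled numbers are 64 and 38. Sidedness is not stated; I take two-sided, since 95% CIs are used. I read SD 10 as the SD of the paired difference.

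**The plan's own figures.** Power comes from the noncentral t with noncentrality δ√n/SD.
- Non-responders, 5 points: 5 × √34 / 10 = 2.92. This gives 80.8% power, so 34 is reproduced, which supports the reading of the SD.
- Responders, 3 points: 3 × √58 / 10 = 2.28. This gives 61.3% power. The same method needs 90 patients for 80%; 58 would follow from an SD of 8. That is a separate issue, carried here only as a sensitivity case.

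**Discordance when the true effects are equal.** The strata are independent, so with powers pR and pN:

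P(exactly one significant) = pR(1 − pN) + pN(1 − pR)

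At 3 points: 0.613 × 0.603 + 0.397 × 0.387 = 0.369 + 0.154 = 0.523.

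| Equal effect (points) | pR (n = 58) | pN (n = 34) | Responders only | Non-responders only | Exactly one |
|---|---|---|---|---|---|
| 0 | 5.0% | 5.0% | 4.8% | 4.8% | 9.5% |
| 2 | 32.2% | 20.5% | 25.6% | 13.9% | 39.5% |
| 3 | 61.3% | 39.7% | 36.9% | 15.4% | 52.3% |
| 4 | 85.0% | 62.0% | 32.3% | 9.3% | 41.6% |
| 5 | 96.3% | 80.8% | 18.5% | 3.0% | 21.5% |

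**Sensitivity at an equal 3 points.** Discordance is 52% at the enrolled 64/38, 46% with SD 8, 42% with SD 14.1 (SD 10 taken as a per-measurement SD, times √2), and 56% with 90/34. Correcting the responder sample size would not remove it.

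**Where the pooled test falls.** In 200,000 simulated trials with equal 3-point effects, the pooled test has 81% power and is significant in 93% of the discordant trials. Discordance without a significant pooled test occurs in about 4% of all trials. Non-responders-only significance without a significant pooled test occurs in about 1.7%.

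**What an estimate of the difference would deliver.**
- SE = 10 × √(1/58 + 1/34) = 2.16 points.
- 95% CI half-width = t(90) × 2.16 = 4.29 points.
- Power for a true 2-point difference (the gap between the two targets, 5 − 3) is about 15%.
- Difference detectable with 80% power: (1.96 + 0.84) × 2.16 = 6.05 points.
- If the effects are equal, this test falsely declares a difference in 5% of trials.

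**The case against.** The strongest reply is that the three questions in the Background each compare directional with ring-mode stimulation within one population, and the planned test in that population answers each of them. None asks whether the effects differ. This stands, and it is why the three tests should remain.

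A reader might infer that the choice between all patients and selected patients will be made from the two stratum p-values alone. The article does not say so. The pooled result and benefit in responders are both stated routes to wider use, and nowhere is significance in one stratum only defined as a difference. Case-based use is not defined as use in non-responders only.

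A reader might also take the 52% as the rate of wrong recommendations. It is not. At an equal 3 points, 37% of trials are significant in responders only, which under the article's own reasoning supports directional review in all patients. Most of the remaining discordant trials have a significant pooled test.

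Two further points carry some weight. The important differences are 3 and 5 points, so an equal 4-point effect could be worthwhile in one group and not the other. That judgement compares each estimate with its own threshold, and it needs neither an interaction nor a contrast of p-values. Also, a fuller protocol or SAP may specify the model term, and readers can derive the difference from the reported stratum results. An unlisted term would be no finding by itself. The point is that the article itself raises differential benefit and offers only separate tests in response.

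**Conclusion.** The point holds in a limited form. The article raises differential benefit and an all-or-case-based conclusion, names three separate uncorrected tests, and describes no estimate of the between-stratum difference and no rule for results that conflict. At the protocol's own 3-point difference, equal effects give discordant stratum results in about 52% of trials.

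It would be tempting to say that this happens about half the time whenever effects are equal. The figures support that only for equal effects of roughly 2.5 to 3.5 points; the rate is 21.5% at 5 points and 9.5% at 0. These values assume two-sided 5% tests, normal paired differences with SD 10 in both strata, and 58 and 34 evaluable patients.

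The within-stratum and pooled tests remain valid for their own questions. What lacks a basis is any statement that responders and non-responders benefit differently.

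**What to change.** - Keep the three planned tests for the three questions in the Background.
- Add a treatment-by-responder-status term to the mixed model already planned. Report the responder-minus-non-responder difference in effect with its 95% CI.
- State that any claim of a different effect in the two groups will rest on this estimate, not on which stratum reached p < 0.05.
- State in advance that the estimate is imprecise (half-width about 4.3 points, about 15% power for 2 points), so a non-significant interaction does not show equal effects.
- Say how a significant pooled result beside one non-significant stratum will be reported.

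The interaction should not become the sole gate to a case-based conclusion. With this precision that would nearly rule the conclusion out, even where responders show no worthwhile benefit.

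The cost is one model term, one table row and a few sentences, with no extra data. The drawback is publishing an openly imprecise estimate.

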## Data Availability

Depending on the type of data and associated privacy regulations, data from the STEERING project will be made publicly available or will become available via the corresponding author, upon reasonable request.

## Abbreviations

CI: Confidence intervals
DBS: Deep brain stimulation
DTI: Diffusor tensor imaging
LED: Levodopa equivalent dose
MDS-UPDRS: Movement Disorders Society Unified Parkinson's Disease Rating Scale
MDS-UPDRS-ADL: Movement Disorders Society Unified Parkinsons' Disease Rating Activities of Daily Living Scale
MDS-UPDRS-MC-A: Movement Disorders Society Unified Parkinson's Disease Rating Scale Motor Complications – Dyskinesias
MDS-UPDRS-ME: Movement Disorders Society Unified Parkinson's Disease Rating Motor Examination Scale
PDQ39: Parkinson’s Disease Questionnaire 39
STN: Subthalamic nucleus
VTA: Volume of tissue activated
